# Post-operative rehabilitation using a digital healthcare system in patients who had undergone rotator cuff repair: protocol for a single-center randomized controlled trial

**DOI:** 10.1186/s13063-022-06648-4

**Published:** 2022-08-17

**Keywords:** Rotator cuff injuries, Postoperative care, Rehabilitation, Augmented reality

## Abstract

**Background:**

Operative repair of a rotator cuff tear requires up to 12 weeks of post-operative (post-op) home-based rehabilitation. Maintaining patients’ compliance in the post-op rehabilitation program is a pivotal component for generating successful outcomes. By developing a post-op rehabilitation-oriented digital healthcare system and applying it in patients who had undergone rotator cuff repair, we aim to increase the efficacy of the rehabilitation program and raise patients’ compliance levels. Here, we present a protocol developed for comparing the efficacy of rehabilitation using a newly developed augmented reality (AR)-based digital healthcare system with that of conventional rehabilitation for post-op rehabilitation of rotator cuff repair.

**Methods:**

This study will recruit a total of 115 patients who had undergone rotator cuff repair within 3 days after surgery. Patients will be randomly allocated to rehabilitation using an AR-based digital healthcare system (digital group) or conventional rehabilitation (conventional group). Patients in both groups will perform brochure-based exercises from the immediate post-op period to post-op 6 weeks. From post-op 6 weeks to 12 weeks, patients in the digital group will use the AR-based system for post-op exercises, whereas patients in the conventional group will continue brochure-based rehabilitation exercises. The primary outcome will be scores on the Simple Shoulder Test at post-op 12 weeks. Secondary outcomes include numeric rating scale scores for pain, measures of range of motion and muscle strength of the affected shoulder, grip strength of the affected arm, scores on the Disabilities of the Arm, Shoulder and Hand test, the Shoulder Pain and Disability Index, and the EuroQoL-5D-5L quality-of-life measure. Analyses will be conducted using an intention-to-treat approach.

**Discussion:**

This study will examine the effectiveness of an AR-based digital healthcare system for post-op rehabilitation in the patients after rotator cuff repair. The study will add evidence for the application of digital healthcare systems in post-op rehabilitation.

**Trial registration:**

ClinicalTrials.gov NCT04511377. Registered on 10 August 2020.

**Supplementary Information:**

The online version contains supplementary material available at 10.1186/s13063-022-06648-4.

## Introduction

Rotator cuff tears result in pain and dysfunction of the shoulder and are one of the most common causes of shoulder disability [1, 2]. Previous studies have estimated the prevalence of rotator cuff tears among the general population at 20% [3] to 23% [4], with a higher prevalence associated with an older age [5]. Treatment of rotator cuff tears can be divided into operative and non-operative treatments. Operative repair of the rotator cuff, which is mainly performed in patients who are unresponsive to conservative management, has demonstrated good results, with reduced pain and good functional recovery of the shoulder [6, 7].

Post-operative (post-op) rehabilitation is a pivotal component of successful rotator cuff repair. The current consensus on rehabilitation after rotator cuff repair suggests 4–6 weeks of immobilization followed by another 4–6 weeks of rehabilitation directed at recovery of range of motion (ROM) and rotator cuff muscle strengthening [8, 9]. Post-op rehabilitation thus takes up to 12 weeks after surgery and is usually performed with outpatient-based or home-based rehabilitation programs. Enhancing the efficacy of the rehabilitation program and improving patient compliance in post-op rehabilitation are important factors for achieving successful outcomes [10]. Thus, various forms of rehabilitation programs, including video instructions [11] and individualized supervision [12], have been attempted to raise patient compliance levels and increase the efficacy of rehabilitation programs.

Recent developments in information and communication technologies have led to attempts to implement virtual reality (VR)- or augmented reality (AR)-based healthcare systems in musculoskeletal post-op rehabilitation [13–15]. These VR- or AR-based rehabilitation programs have shown advantages in terms of increasing patients’ compliance levels and documenting their progress [16, 17], essential factors for successful post-op rehabilitation. However, most previous studies have used commercial healthcare applications or devices providing generalized fitness exercise programs rather than rehabilitation-oriented programs. Developing and applying an AR-based digital healthcare system with post-op rehabilitation-oriented programs for patients who had undergone rotator cuff repair would increase the efficacy of rehabilitation and improve patient compliance. In this report, we present a protocol for evaluating the efficacy of an AR-based digital healthcare system for post-op rehabilitation of rotator cuff repair by comparing it with that of a conventional rehabilitation program in an assessor-blinded 1:1 randomized controlled single-center trial.

## Methods

### Study design

This protocol was developed for an assessor-blinded superiority randomized controlled trial. The eligible participants are recruited 1–3 days after surgery at the orthopedic ward of Seoul National University Bundang Hospital (Seongnam-si, Gyeonggi-do, Korea). The participants are then randomized based on 1:1 allocation to two groups: the digital group will undergo a rehabilitation program using a digital healthcare system, whereas the conventional group will undergo a conventional rehabilitation program. Patients will be discharged home a few days after the surgery with a shoulder brace on the affected shoulder and will immediately begin the rehabilitation program, including early mobilization of the shoulder girdle. Until post-op 6 weeks, when they will remove their braces, both groups will use brochures received at the time of discharge that provide instructions on mobilizing the affected shoulder girdle. From post-op 6 to 12 weeks, participants in the digital group will perform exercises using an AR-based digital healthcare system (UINCARE Home+; UINCARE Corp., Seoul, Korea), whereas participants in the conventional group will perform exercises using only the brochures provided by the hospital. Participants in both groups will be allowed hospital visits for exercise education by physical therapists, up to three sessions (30 min per session) over 12 weeks. The primary and secondary outcomes will be measured at baseline and at post-op 6, 12, and 24 weeks. An overview of the study design and process is given in Fig. 1.

**Fig. 1 Fig1:**
[figure not shown]
Study flow diagram

### Participants and recruitment

In the protocol, the aim is to enroll 115 adult participants over 50 years of age who had undergone rotator cuff repair surgery. Patients who had undergone biceps tenotomy, acromioplasty, or labral repair along with the rotator cuff repair can be included. Patients who had undergone reverse total shoulder arthroplasty or total shoulder arthroplasty will be excluded. Patients who are not discharged home or who cannot understand or read Korean will also be excluded. Other major inclusion and exclusion criteria are described in Table 1. Participants will be recruited from the orthopedic surgery ward at 1–3 days after surgery by research therapists from the study team. The research team will screen the medical records of the post-op patients for eligibility, and the eligible patients will receive written and verbal information about the trial from the research therapists, along with a request to participate.

**Table 1 Tab1:** Major inclusion and exclusion criteria

**Inclusion criteria**	
1. Over 50 years of age	
2. Had rotator cuff repair surgery	
3. Discharged home after surgery	
**Exclusion criteria**	
1. Previous history of shoulder surgery on the affected shoulder	
2. Severe neurological deficit or infection in the affected shoulder	
3. Severe comorbidities (e.g., uncontrolled diabetes mellitus or rheumatoid arthritis) that will inhibit rehabilitation	
4. Cannot participate in the rehabilitation program	

### Randomization and blinding

Participants will be randomized after the baseline evaluation and allocated to either the Digital or conventional group at a 1:1 ratio. Randomization sequences will be computer-generated blocks, without stratification, by the institution’s biostatistician, who is independent of the study team. The randomized allocation information was sealed in a numbered opaque envelope. The envelope seals will be checked monthly by the principle investigator to make sure the future participants’ allocation is kept blinded. Participant allocation and follow-up arrangements will be managed by the study coordinator, who will not be blinded to the participants’ group assignments. Assessments will be performed by two research therapists from the study team, who will be blinded to the participants’ intervention groups.

### Intervention

#### Conventional group

Participants in this group will undergo a brochure-based home rehabilitation program, which is the standard protocol for patients who had undergone rotator cuff repair surgery in our hospital. The rehabilitation program can be divided into three phases: on-brace, off-brace, and active mobilization. The on-brace phase (immediate post-op period to post-op 6 weeks) mainly consists of low-intensity whole-body exercises with shoulder girdle, elbow, and hand mobilization exercises on the affected side. Participants in this phase are instructed to perform three sets of exercises with 10 repetitions of each set per day. The off-brace phase (post-op 6–9 weeks) consists of passive shoulder ROM exercises using an exercise stick and an early scapular stabilization exercise. The active mobilization phase (post-op 9–12 weeks) consists of both active and passive shoulder ROM and scapular stabilization exercises. During the off-brace and active mobilization phases, patients are instructed to perform 3–5 sets of exercises with 10 repetitions of each set per day. A detailed exercise protocol is described in Table 2.

**Table 2 Tab2:** Exercise protocols for post-op rehabilitation in patients who had undergone rotator cuff repair

Phase	Exercise		Description
On-brace (immediate post-op period to post-op 6 weeks)	Whole-body exercise	Lunge	
		Trunk rotation	
	Upper extremity mobilization	Finger/wrist/elbow ROM exercises	
		Shoulder shrugging	
Off-brace (post-op 6–9 weeks)	Passive ROM	Forward flexion (supine)	Hold a stick with both hands and move it in both directions using the non-affected arm to passively stretch the affected arm.
		Horizontal abduction (supine)	
		External/internal rotation (supine)	
	Early scapular stabilization	Lower trapezius exercise	Retract and depress the scapula with both hands while holding a towel at both ends.
		Low rowing exercise	Place the palm (affected side) on the wall and try to retract and depress the scapula.
Active mobilization (post-op 9–12 weeks)	Active (assisted) ROM	Forward flexion (supine)	Perform active ROM exercise of the affected arm with help from the unaffected arm.
		Internal rotation (supine)	
		External rotation (standing, 90° abducted)	Gently lean against the wall with the affected shoulder externally rotated in 90° abduction.
		Forward flexion by sliding against a wall	Forward flex the affected arm by sliding along the wall with help from the unaffected arm.
	Scapular stabilization	Rowing exercise	Forward flex the shoulder to 45° and then retract the scapula with a backward pulling motion
		Punching exercise	Retract the scapula by pulling the shoulder backward and punching out straight ahead to protract the scapula.
		Threading exercise	Flex the affected-side elbow to 90° and abduct the shoulder to 45°. Rotate the trunk to the unaffected side keeping the elbow and shoulder angles fixed.
		Lawn-mower exercise	Stand with the feet shoulder-width apart, bend the trunk to the unaffected side. Reach out the affected arm toward the contralateral knee and then return to the normal position by retracting the scapula.

Participants in the conventional group will be educated by a physical therapist, and a brochure with illustrations of the exercises will be provided before they are discharged home. Additional exercise education sessions will be allowed (up to three times, 30 min per session) at the participants’ request.

#### Digital group

The rehabilitation program for participants in this group employs a digital healthcare system. During the on-brace phase, participants in this group will use the same brochure as the conventional group participants for home-based rehabilitation. Participants in the digital group will also be educated by a physical therapist before being discharged home. During the off-brace and active mobilization phases, participants will use the digital healthcare system for home-based rehabilitation. The digital healthcare system consists of four components: software for the rehabilitation program, a three-dimensional (3D)-depth camera (Xbox One Kinect for Windows®, Microsoft, USA), a computer, and a display (TV or monitor). The software consists of an AR-based program for post-op rotator cuff tear rehabilitation, and the 3D camera tracks the participant’s motion until it reaches a pre-determined angle or position. The rehabilitation program and prescribed exercises will be matched with those for the conventional group. Participants in the digital group will use this system at home during post-op 6–12 weeks. The daily exercise amount and progression will be logged by the system, and physicians will review the data at the outpatient clinic. Up to three additional exercise education sessions (30 min each) will also be allowed in this group upon participants’ request.

### Outcomes

#### Primary outcome measure

The primary outcome will be scores on the Simple Shoulder Test (SST), which range from 0 (worst) to 12 (best). The SST is a self-reported questionnaire consisting of 12 dichotomous (yes/no) questions that measure functional limitations [18]. It is a widely used outcome measure for assessing functional improvement in patients who had undergone rotator cuff repair [19, 20].

#### Secondary outcome measures

A number of secondary outcome measures will be employed (Table 3). Pain at rest and during activity will be measured using a numeric rating scale (0–10), and the ROM of the affected shoulder will be measured manually by a research therapist. The shoulder ROM will be measured in degrees in four directions: forward flexion (0–180°), abduction (0–180°), external rotation (0–90°), and internal rotation (0–70°). Muscle strength of the affected shoulder in four directions will be measured by the research therapist using a manual muscle test and rating scale (0–5). Hand grip strength on the affected side will be measured using a Takei handgrip dynamometer (Takei Scientific Instruments Co., Ltd., Tokyo, Japan). Shoulder function will be assessed using the Disabilities of Arm, Shoulder and Hand (DASH) questionnaire and the Shoulder Pain and Disability Index (SPADI). DASH is a 30-item questionnaire that measures the ability of a patient to perform certain upper extremity activities. Scores range from 0 to 100, with a score of 0 indicating no disability and 100 indicating the most severe disability. The SPADI (0–100) consists of a pain scale and a disability scale; higher scores indicate more pain and greater disability. Quality of life will be measured using the European Quality of Life Index (EQ-5D-5L).

**Table 3 Tab3:** Timetable and measures to be made

	Screening	Post-operation week(s)		
	Baseline	6	12	24
**Primary outcome measure**				
Simple Shoulder Test	X	X	X	X
**Secondary outcome measures**				
Pain at rest and action (NRS)	X	X	X	X
ROM of affected shoulder	X	X	X	X
MMT of affected shoulder	X	X	X	X
Grip strength (JAMAR dynamometer)	X	X	X	X
Function outcomes				
DASH score	X	X	X	X
SPADI score	X	X	X	X
Quality of Life: EQ-5D-5L	X	X	X	X
**Other measures**				
Demographic information	X			
Medical History	X			
Rotator cuff tear size	X			
User satisfaction questionnaires^a^			X	X

*NRS* numeric rating scale, *ROM* range of motion, *MMT* manual motor test, *DASH* disabilities of the arm, shoulder and hand, *SPADI* shoulder pain and disability index, *EQ-5D-5L* European Quality of Life Index

^a^Digital group only

### Sample size

A minimal clinically important difference (MCID) in scores on the SST in patients with rotator cuff tear was reported to be 4.3 [21], and the average score on the SST at post-op 3 months in a previous study was 6.34 (SD = 3.7) [22]. The minimum sample size for the present study was calculated *t*-test based on a 2.15-point difference in SST score (50% of the MCID) and an SD of 3.7, while allowing a 5% probability of two-sided type 1 error and applying 80% statistical power. Forty-nine subjects will be required in each group to allow 15% attrition per group; thus, a total of 115 subjects will be required for the study.

### Data management and sharing

All participant data will be collected by research team members and will be stored in the secured network of Seoul National University Bundang Hospital. Backup database will be updated regularly and only the research team will have access to the database. The case report forms will be stored in the locked cabinet of the research team. The coordinating investigator will have access to the final study dataset and the anonymized dataset will be available on request to the corresponding author. Final results will be published in peer-reviewed journals and presented at conferences, both nationally and internationally after completion of the study.

### Primary hypothesis and data analysis

The primary hypothesis is that participants in the rehabilitation program using a digital healthcare system will demonstrate better shoulder function compared to those in the conventional rehabilitation group. Analyses will be performed using both intention-to-treat and per-protocol approach. The primary outcome measure for this study will be SST scores at post-op 12 weeks. A two-way repeated-measures ANOVA will be used to explore the effects of intervention, time, and intervention by time interaction on SST scores. The results will be presented with a mean difference with 95% confidence interval at each follow-up time point. Continuous secondary outcomes will be analyzed using repeated-measures ANOVA at each post-op 12 weeks and 24 weeks. Subgroup analysis based on the size of the tear will be performed only if there are sufficient participants in all four subgroups (small, <1 cm; medium, 1–3 cm; large, 3–5 cm; massive, ≥5 cm tear or more than two tendons involved) [23]. Statistical analysis will be performed after the 24-week follow-up measurement of the last enrolled participant is done and no inter-rim analysis will be performed during the trial. All tests will use a 5% level of significance (*P* < 0.05).

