### Participant safety and withdrawal

The potential risks for participants in this study are minimal. There is no independent oversight committee and adverse events (AEs) will be monitored by the research team at the scheduled follow-ups. Possible AEs include increased pain due to exercise and re-tear of the repaired rotator cuff tendons. Pain will be managed at the orthopedic outpatient clinic with pain medications or steroid injections, if needed. Surveillance of re-tear of repaired tendon will be routinely performed in post-op 12 weeks; however, if the re-tear is clinically suspected at any time during the follow-up periods, appropriate examinations and treatments will be provided. Participants in both groups can report AEs to the research team via direct telephone contact. Participants in the digital group will also receive a telephone number of the manufacturer for technical support.

Participants are allowed to leave the trial at any time. Participants can withdraw from the trial by informing the research team. Participants will be encouraged to visit the pre-scheduled follow-ups even if they withdraw from the study for data collection. Participants in both groups will be regularly reminded with phone calls and text messages to minimize loss of follow-ups and maximize the adherence to the trial.

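### Repeated-measures ANOVA in its standard form does not deliver the promised intention-to-treat analysis when visits are missed, and the methods do not rank intention-to-treat above per-protocol

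*Protocol article*

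**What the plan says.** On the analysis population, the section on the primary hypothesis and data analysis says: "Analyses will be performed using both intention-to-treat and per-protocol approach". The Methods paragraph of the abstract says: "Analyses will be conducted using an intention-to-treat approach". The design is superiority: "This protocol was developed for an assessor-blinded superiority randomized controlled trial".

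On the endpoint and model, the same analysis section says: "The primary outcome measure for this study will be SST scores at post-op 12 weeks". The model follows: "A two-way repeated-measures ANOVA will be used to explore the effects of intervention, time, and intervention by time interaction on SST scores". The study design section fixes the occasions: "The primary and secondary outcomes will be measured at baseline and at post-op 6, 12, and 24 weeks".

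On incomplete data, the sample size section says: "Forty-nine subjects will be required in each group to allow 15% attrition per group", giving a total of 115. It does not say by which visit the 15% accrues. The section on safety and withdrawal says: "Participants will be encouraged to visit the pre-scheduled follow-ups even if they withdraw from the study for data collection". The article states no imputation rule and no mixed-model version of the ANOVA. It also does not say that incomplete participants will be dropped.

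**The concern.** Four commitments pull against each other: intention-to-treat, a week-12 primary endpoint, an ANOVA over repeated occasions, and an expected 15% attrition. A classical two-way repeated-measures ANOVA needs a complete row of scores for each participant. Someone who attends week 12 and misses only week 24 can therefore drop out of the comparison the trial was designed to make, although the primary score was observed. The effort to keep seeing people after withdrawal is also partly wasted, because one missed visit removes all their scores.

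Two things are at stake. The first is precision: the sample size rests on a t-test, which would use everyone seen at week 12, while the ANOVA uses only those seen at every modelled visit. The second, and more important, is selection. Participants know their arm (only assessors are blinded), the SST is self-reported, and re-tear surveillance takes place at week 12. Missing week 24 could plausibly be related to function at week 12. If that relation differs between arms, the week-12 contrast among complete cases is distorted.

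The unranked pair of populations adds an ambiguity. In a superiority trial the reader should know in advance which result tests the primary hypothesis.

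**Working it through.** **1. The plan's own figure.** Inputs from the sample size section: difference 2.15, SD 3.7, two-sided 5%, power 80%, attrition 15%.

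- Standardised difference: 2.15 / 3.7 = 0.581.
- Normal approximation: 2 × (1.960 + 0.842)² / 0.581² = 46.5, so 47 per arm. The exact t-test gives 47.5, so 48 per arm. The stated 49 is within two.
- Attrition: 2 × 49 / 0.85 = 115.3, stated as 115.

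The figure reproduces. The plan budgets for about 98 evaluable participants.

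**2. Power if only complete cases are used.** This is exact t-test power at 0.581. The first row takes 15% as the total loss through week 24. The other rows are assumptions.

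| Share lacking at least one modelled score | Complete cases of 115 | Per arm | Power |
|---|---|---|---|
| 15% | 97.8 | 48.9 | 81.2% |
| 20% | 92.0 | 46.0 | 78.7% |
| 25% | 86.3 | 43.1 | 76.0% |

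The 80% line is crossed when complete cases fall below 2 × 47.5 = 95, a loss of 1 - 95/115 = 17%. For comparison, if 10% are lost by week 12 and 20% by week 24, using everyone seen at week 12 gives 83.3%, against 78.7% for complete cases.

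**3. Bias in the week-12 difference.** All of this is assumption, because the article gives no information on the mechanism. Let every week-12 score be observed, treat it as normal with SD 3.7 (an approximation for a 0-12 scale), and let z be the standardised score. The probability of missing week 24 is logistic: 10% or 15% at z = 0, with the odds multiplied by 2.7 for each SD lower. The shift in an arm's complete-case mean is 3.7 × E(z | retained).

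- *Digital arm only.* E(z | retained) is 0.119 at 10% and 0.164 at 15%, so the difference shifts by 3.7 × 0.119 = +0.44 and 3.7 × 0.164 = +0.61. That is 20% to 28% of 2.15. By symmetry, loss of this kind in the conventional arm only would give -0.44 to -0.61.
- *Both arms, z measured from each arm's own mean.* Both means move equally, so the bias is about 0.
- *Both arms, loss depending on the absolute score, true difference 2.15.* With z measured from the conventional mean, the digital arm sits 0.581 SD higher and loses fewer people. The difference shifts by -0.16 to -0.20.

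A separate simulation of the digital-only case (57 per arm, about 15% missing week 24) gave 2.62 among complete cases against 2.16 in all participants, a shift of +0.46. With random loss the two agreed (2.19 and 2.18).

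In each of these examples missingness depends only on an observed week-12 score, so a likelihood model using all available scores would not carry the bias.

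**4. The two statements on population, side by side.** The abstract has intention-to-treat only. The methods have intention-to-treat and per-protocol, unranked. Intention-to-treat is in both; per-protocol is missing from the abstract; neither says which analysis decides the primary hypothesis.

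**The case against.** A reader might infer that the trial is in fact a complete-case analysis under an intention-to-treat label. The article does not support that. It nowhere says that incomplete participants are deleted. ANOVA and intention-to-treat are compatible if missing scores are imputed, and imputation may be set out in the full protocol (version 3.0) or an analysis plan, neither of which is shown. Silence on that detail in a condensed article is not itself a fault. The article also does not say which visits enter the SST model. The sentence on secondary outcomes, which refers to weeks 12 and 24 in turn, could be read as separate models up to each time point. On that reading, missing only week 24 would not cost a participant the week-12 comparison.

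A reader might also infer that abstract and methods name rival deciding populations, leaving a free choice of the favourable result. They do not: both include intention-to-treat, neither names a deciding set, and the methods commit to running both analyses.

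On size, the 15% allowance may already cover loss through week 24, in which case power stays above target. The upward bias needs function-related loss confined to the digital arm, and the article gives no particular reason to expect that: device use ends at week 12 and reminders go to both groups.

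These points limit the claim to a conditional one and remove any single figure for bias. What stands is that the method actually named, in its usual form, does not fit the stated population when missing visits are expected, and that the methods leave the two populations unranked.

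**Conclusion.** The point holds conditionally and merits a change before analysis. Without imputation or a mixed-model version, the named ANOVA excludes any participant missing a modelled visit and so does not deliver the stated intention-to-treat analysis. The unranked populations are an ambiguity in the methods and an omission in the abstract, not a contradiction over which analysis decides the trial.

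Power is the lesser part: about 81% if total loss is the planned 15%, and 76-79% only if 20-25% lack at least one score. Bias has no fixed sign or size. The range runs from about +0.4 to +0.6 points (digital-arm loss only), through about 0, to about -0.15 to -0.2 (loss by absolute score in both arms), and each value rests on the missingness mechanism assumed. It would be wrong to report the upward figure alone as the expected distortion.

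**What to change.** Replace the repeated-measures ANOVA for SST with a likelihood-based (REML) mixed model for repeated measures. It should use every available post-randomisation SST score, including those collected after withdrawal, with the week-12 between-arm contrast and its 95% confidence interval as the primary result. Name intention-to-treat (all randomised participants, as allocated) as the primary analysis and per-protocol as supportive, unable to replace it. Make the abstract agree with the methods.

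The model assumes that missingness depends only on observed data, and it cannot recover an outcome for someone with no post-randomisation score. Multiple imputation would be another way to keep partly observed participants. The mixed model is the simpler choice here and still gives the mean differences by visit that the article promises.

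The cost is a small change of wording and slightly more modelling work, with no new data, visits or participants. The article schedules analysis only after the last 24-week visit and plans no interim look, so the change can be made before any comparison is run.

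### Week-12 SST is the primary outcome and the basis of the sample size, but the week-12 difference is never named as the primary test; the only named test is a repeated-measures ANOVA whose effects are different quantities

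*Protocol article*

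**What the plan says.** Under Primary hypothesis and data analysis, the article fixes the endpoint: "The primary outcome measure for this study will be SST scores at post-op 12 weeks". The test named for SST follows: "A two-way repeated-measures ANOVA will be used to explore the effects of intervention, time, and intervention by time interaction on SST scores". The next sentence adds: "The results will be presented with a mean difference with 95% confidence interval at each follow-up time point". The section sets a 5% level for every test. It does not say which ANOVA effect or visit decides the superiority question, and the primary hypothesis there speaks of better shoulder function without a time point.

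Under Sample size, the calculation is a t-test "based on a 2.15-point difference in SST score (50% of the MCID) and an SD of 3.7", two-sided 5%, 80% power, with the SD taken from a study reporting SST at 3 months after surgery. It gives 49 per group and 115 in total with 15% attrition.

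Under Study design: "The primary and secondary outcomes will be measured at baseline and at post-op 6, 12, and 24 weeks". The analysis section does not say which of these visits enter the ANOVA. The arms are treated alike at first: "Until post-op 6 weeks, when they will remove their braces, both groups will use brochures received at the time of discharge". The Digital group section confirms this: "During the on-brace phase, participants in this group will use the same brochure as the conventional group participants for home-based rehabilitation".

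**The concern.** The endpoint and the sample size concern one number, the difference between groups at week 12. A two-way repeated-measures ANOVA over the scheduled visits tests other things. Its intervention effect is the group difference averaged over visits, and those include one or two visits at which the groups have not yet been treated differently. Its interaction asks whether the group difference varies over time in any way, without direction and without singling out week 12.

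The main conclusion of a superiority trial is at stake. If the interaction is significant but the week-12 interval includes zero, or the reverse, the article does not say which result governs. All analysis takes place after the last 24-week visit, so without a rule that choice could be made with every result in view.

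**Working it through.** **Inputs from the article.** Difference δ = 2.15, SD σ = 3.7, two-sided α = 5%, n = 49 per group; measurements at baseline and weeks 6, 12 and 24; same care in both arms until week 6.

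**Assumptions not in the article.** Exchangeable within-patient correlation ρ = 0.3, 0.5 or 0.7; SD 3.7 at every visit; no group difference at baseline or week 6; at week 24 the 2.15-point effect is either fully kept or gone.

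**1. Reproducing the design.** n = 2(1.96 + 0.842)² × 3.7² / 2.15² = 46.5, so 47 per group; the exact t calculation gives 47.5, so 48. The stated 49 is close. At 49, the standard error is 3.7 × √(2/49) = 0.748 and the noncentrality is 2.15/0.748 = 2.88, giving **81.3%** power. With attrition, 98/0.85 = 115.3, in line with 115. The design figures therefore belong to the week-12 contrast.

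**2. Intervention main effect.** With k visits this is a t-test on each patient's mean, with standard error √{2σ²[1 + (k−1)ρ]/(kn)}. Example, four visits, effect kept, ρ = 0.5: mean difference (0 + 0 + 2.15 + 2.15)/4 = 1.075; standard error √(2 × 13.69 × 2.5/(4 × 49)) = 0.591; noncentrality 1.82; power 44%.

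| Visits in model | Week-24 effect | ρ = 0.3 | 0.5 | 0.7 |
|---|---|---|---|---|
| Four | kept | 54% | 44% | 37% |
| Four | gone | 18% | 15% | 13% |
| Three post-op | kept | 74% | 64% | 57% |
| Three post-op | gone | 26% | 21% | 19% |

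**3. Interaction.** The noncentrality is λ = (n/2) × SS/[σ²(1−ρ)], where SS is the sum of squares of the visit differences about their mean. Four visits give F on 3 and 288 df.
- Effect kept: SS = 4 × 1.075² = 4.62; at ρ = 0.5, λ = 24.5 × 4.62/6.845 = 16.5. Power is 83%, 94% and 99.6% for ρ = 0.3, 0.5 and 0.7.
- No difference at week 12, 2.15 points at week 24 only: SS = 0.75 × 2.15² = 3.47; at ρ = 0.5, λ = 12.4. The test is significant in 70%, 85% and 98% of trials.
- A difference at week 12 only has the same SS, hence exactly the same power. The interaction cannot tell these two cases apart.

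**4. Type I error.** Each F-test alone keeps 5%. If either may count as success, the error is 1 − 0.95² = 9.75% (simulated 9.7%, 8,000 runs, ρ = 0.5). If the week-12 interval may count too, it is about 12% (same simulation). The week-12 test alone has 5%.

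**The case against.** The strongest reply is that the week-12 comparison is in the plan. The article promises a mean difference with 95% CI at each follow-up, week 12 is one of those, and a 95% interval is equivalent to a two-sided 5% test of the sized contrast. This stands. A reader might infer that the trial never makes the comparison it was powered for, or that the stated 80% power and 5% error do not apply. The document does not support that: both apply to the week-12 interval. What is missing is its designation as the deciding result.

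Second, the ANOVA is described as exploring effects and is not called the primary test, so one may read it as describing the time course. That is a fair reading, but it leaves the primary outcome with no named test at all.

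Third, the ANOVA's visits are inferred from the schedule. With only baseline and week 12 in the model, the 1-df interaction is the group difference in change to week 12, and at ρ = 0.5 its power equals the t-test's 81.3%. The text does not exclude this, nor does it say so, and that interaction would still need to be named as decisive.

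Fourth, the size of the loss depends on assumptions. With smaller early SDs (1.0, 2.5, 3.7, 3.7) and a kept effect, simulated main-effect power over four visits rises to 58-79%. A reader might also count both F-tests and all three visit-wise intervals as routes to success, which gives about 15-17% error with equal SDs. The article states no rule under which five results count, and week 6 precedes use of the digital system, so that figure should not be charged to the plan.

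**Conclusion.** The concern holds in limited form. The named test does not match the endpoint or the sample-size calculation, and the contrast that does match is reported without priority. If the ANOVA covers the scheduled visits, the main effect falls short of the 80% target in every case examined: with equal SDs, 37-74% if the benefit is kept and 13-26% if it is gone by week 24. The interaction is often well powered but can be significant with nothing happening at week 12. Error inflation to about 10% or 12% arises only if more than one result may count as success, a question the article leaves open. The exact sizes rest on the assumed correlations, SDs and week-24 effect; that neither effect is the week-12 difference does not. This goes beyond detail that an article may leave to an analysis plan, because the method it does state answers a different question from the one the trial was sized for.

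**What to change.** Name one primary analysis. For example: the primary analysis is the digital minus conventional difference in SST at post-op week 12, adjusted for baseline SST, with 95% CI and a two-sided 5% test. It may come from a mixed model for repeated measures on the post-operative visits or from an ANCOVA at week 12; either serves, and the choice matters less than naming one. State that the overall group effect, the interaction and the 6- and 24-week differences are supportive and carry no claim of superiority on their own, and list the visits that enter any repeated-measures model.

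The cost is a change of wording in the protocol and analysis plan, made before the data are analysed; no interim analysis is planned. No new data or patients are needed: 49 per group already gives 81.3% power for an unadjusted week-12 comparison, and baseline adjustment would be expected to add to that.
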